**Effectiveness**		
SBP outcomes	Mean value in change with fully adjustment model	95% confidence interval for non-adjusted and fully adjusted
QALY outcomes	Mean value in change with fully adjustment model	95% confidence interval for non-adjusted and fully adjusted
**Cost**		
Compensation for village doctors	Recorded headcount cost	Fidelity rate of follow-up visits ranging from lowest value to 100%
Missing information of inpatient care for those who were hospitalized in other healthcare facilities.	Median inpatient cost for same or similar diagnosis	25%, 75% percentile of inpatient cost for those who were hospitalized with same or similar diagnosis.
Missing information of outpatient cost which is not covered by health insurance.	Mean outpatient cost for same or similar diagnosis	25%, 75% percentile of outpatient cost for those who were hospitalized with same or similar diagnosis.
Missing information on medication cost of daily doses.	Mean cost for the conventional drugs	25%, 75% percentile of medication cost for those who took same or similar drugs.
Development cost of the digital health system	None	Development costs of the SINEMA model when the cost was shared by years of follow-up

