**Medical costs (for both intervention and control arm)**				
Inpatient cost	Time, human resources, facilities used for inpatient care	Mean days of stay and frequency of hospitalization within trial period	Mean cost replacement value recorded in social medical scheme	Reimbursement system
Outpatient cost	Time spent in delivering care	Number of follow-up visits	Replacement value converted to annual equivalent cost	(Estimated)
Medication cost	Self-reported medication use	Number of medications used and adherence rate	Replacement value converted to annual equivalent cost based on local medication price list	Follow-up survey

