Our study design has several unique features. First, the study measures a multifaceted intervention with digital health components. Digital health interventions have a high potential to deliver interventions to a large-scale population, thus, it holds the promise of improving chronic disease management. Second, compared to human-delivered intervention, the development cost for digital health intervention is relatively high; however, the operation and marginal cost for the implementation could be limited to none if it is scaled to a large population (25). In our protocol, we followed previous studies' methods to evaluate the operational cost of the SINEMA model in our design (11). We also include the development cost in our sensitivity analysis.

As for data collection, due to the constrained funding support, the SINEMA trial observed and measured the cost and effectiveness of the intervention over a 12-month period. Although such follow-up duration was reasonable to measure a high number of stroke cases, the data collected from the trial period hardly provided information about the long-term benefits and impact of the intervention. Instead, we will use data from other trials and cohort studies that were conducted in similar settings to estimate the long-term natural transition of stroke patients in rural China (26, 27). This approach enables us to estimate the long-term economic impact of the SINEMA intervention.

The main limitation of this design lies in the field of cost measurement. First, although we measured key direct health costs at the individual level, we are only able to quantify the inpatient costs and medication costs for participants from the health insurance data. Due to the limited data access, we cannot measure the cost of inpatient care if the patients seek healthcare services beyond the major four hospitals in the study regions, which is likely to happen as there is no referral system that restricts service-seeking behaviors in rural China (27). Therefore, we tend to underestimate the inpatient costs if there are relatively more inpatients in the control group. Second, the analysis may underestimate some of the labor costs. For instance, the village doctors may provide blood pressure assessments during clinic visits for free, and the payment scheme may not be set by the number of services provided at the clinic visits. These visits were not paid, thus were not included in the financial analysis.

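### Table 2 fills unobserved inpatient costs with a median where the ICER needs a mean, so under right-skewed costs the base case is biased low on average

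*Protocol article*

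**What the plan says.** The rule stands in the Cost block of Table 2. The row headed "Missing information of inpatient care for those who were hospitalized in other healthcare facilities" has the base case "Median inpatient cost for same or similar diagnosis" and the range "25%, 75% percentile of inpatient cost for those who were hospitalized with same or similar diagnosis".

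The comparable entries use means:
- Missing outpatient cost (Table 2): "Mean outpatient cost for same or similar diagnosis".
- Missing medication cost (Table 2): "Mean cost for the conventional drugs".
- Valuation of inpatient cost (Table 1): "Mean cost replacement value recorded in social medical scheme".

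No reason is given for using a median in the one row. Under Data analysis, the ICER is the between-arm difference in cost divided by the between-arm difference in effect, and costs are to be modelled with a gamma distribution and log link. The Discussion concedes that "we cannot measure the cost of inpatient care if the patients seek healthcare services beyond the major four hospitals" and calls such care likely, but does not say how common it is.

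The outpatient row takes its range from "25%, 75% percentile of outpatient cost for those who were hospitalized with same or similar diagnosis", whereas its base case carries no restriction to hospitalised patients.

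**The concern.** Only an arithmetic mean, multiplied by the number of admissions, gives back total spending. A cost difference meant for a health-system decision therefore has to be a difference in means. Inpatient costs usually have a long right tail, and the plan's own cost model assumes one. The median leaves that tail out, although the expensive admissions are part of what the payer spends.

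The Introduction reports relative reductions of 35-55% in a group of outcomes that includes hospitalisation. Avoided admissions are thus a likely source of savings. If some of them are valued too low, the saving credited to the intervention shrinks, and cost per QALY moves up against the threshold of 1.5 times GDP per capita.

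**Working it through.** The plan states no cost figure, CV or imputed share, so it has no figure of its own to reproduce. The check asks how far a median lies below the mean under the plan's cost family, with a log-normal as a second right-skewed shape.

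**Inputs**
- Median as fill: Table 2.
- Gamma cost distribution: Data analysis.
- CV of cost within a diagnosis group: assumed 0.5, 1.0 and 1.5.
- Share *f* of true inpatient cost that is imputed: assumed 10%, 30% and 50%.

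**Step 1: median relative to mean**
- Gamma: shape k = 1/CV², mean scaled to 1, median found numerically. At CV 1.0 it is ln 2 = 0.693.
- Log-normal: σ² = ln(1 + CV²), so median/mean = exp(−σ²/2) = 1/√(1 + CV²). At CV 1.0 it is 1/√2 = 0.707.

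| CV | Median/mean, gamma | Median/mean, log-normal | Imputed part too low by |
|---|---|---|---|
| 0.5 | 0.918 | 0.894 | 8-11% |
| 1.0 | 0.693 | 0.707 | 29-31% |
| 1.5 | 0.407 | 0.555 | 45-59% |

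**Step 2: effect on total inpatient cost**

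Understatement = *f* × (1 − median/mean).

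| CV | *f* = 10% | *f* = 30% | *f* = 50% |
|---|---|---|---|
| 0.5 | about 1% | 2-3% | 4-5% |
| 1.0 | 3% | 9% | 15% |
| 1.5 | 4-6% | 13-18% | 22-30% |

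Example: CV 1.5, *f* = 30%, gamma: 0.30 × (1 − 0.407) = 0.178.

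**Step 3: direction in the ICER numerator**

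Let a and b be the mean number of imputed admissions per participant in the intervention and control arms, with the same cost distribution in both, mean μ and median m. The error in incremental cost is (a − b)(m − μ). Under right skew m − μ is negative. If b exceeds a, the product is positive and incremental cost is overstated. If a equals b, the error cancels. The offset from these admissions is (b − a)μ in truth and (b − a)m as planned, so it is understated by the percentages in step 1, whatever the size of the reduction.

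**Step 4: does the planned range reach the mean?**

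25th and 75th percentiles relative to the mean:
- CV 0.5: 0.63-1.28 (gamma), 0.65-1.23 (log-normal).
- CV 1.0: 0.29-1.39 and 0.40-1.24.
- CV 1.5: 0.08-1.29 and 0.27-1.15.

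The range contains the mean in each case. The 75th percentile falls below the mean only when CV exceeds about 2.07 (gamma) or 2.27 (log-normal).

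**The case against.** Several points on the other side stand.

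**The size is unknown.** What matters is the skew within a diagnosis group. The gamma model does not fix it, because a gamma with small CV is nearly symmetric. At CV 0.5 with 10% imputed, total inpatient cost is off by only about 1%. The Discussion calls out-of-area care likely, which does not establish that it is frequent.

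**The quartile range is defensible.** A reader might infer that the range misses the true mean, or that it is an error because it is not a confidence interval. Step 4 does not support the former at plausible skew. On the latter, Data analysis gives the deterministic runs the task of finding key determinants, and it plans scatterplots and an acceptability curve as well. A wide scenario range suits that task. A 95% CI of the donors' mean would cover only sampling error in the four hospitals, not the possibility that admissions elsewhere cost more or less. The 75th-percentile run also tests a value above the mean, which partly offsets the low base case.

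**Not every admission is undervalued.** A median is too high for about half of individual admissions. The bias is in the average.

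**The Discussion does not contradict Table 2.** A cost that cannot be measured can still be imputed.

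**The likely direction is against the intervention.** The fill would not by itself create a false claim of cost-effectiveness. Even that direction is an inference, since the reported fall in hospitalisation is not broken down by place of admission.

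None of this justifies a median in the base case. Robustness to outliers is no answer when the quantity wanted is the mean, and the adjacent rows already use it.

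**Conclusion.** The inpatient row is wrong as written and should be fixed. Under right-skewed costs the sign of the average error is known: the imputed cost is too low. Its size depends on two quantities that the documents do not give. Under the assumptions shown, total inpatient cost is understated by about 1% (CV 0.5, 10% imputed) to 13-18% (CV 1.5, 30% imputed), and by more if a larger share is imputed. Incremental cost is overstated only if the control arm has more imputed admissions, which the reported reduction in hospitalisation suggests but does not show.

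This does not amount to a must-fix: the effect may be small, it probably works against the intervention, and the planned range reaches above the mean at moderate skew.

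A secondary point is the outpatient row, whose base case and range refer to differently described groups. The wording may have been carried over from the row above. As it stands, the base case need not lie within its own range.

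**What to change.** 1. In the inpatient row of Table 2, replace the median with the arithmetic mean for the same or similar diagnosis. A model-based mean or multiple imputation from the planned gamma model is an alternative. That model adjusts for length of stay, which would then have to be known or imputed for these admissions.
2. Keep the 25th and 75th percentiles if wanted, labelled as a scenario range. A 95% CI of the mean is an optional addition.
3. In the outpatient row, use the same donor group for base case and range.

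The cost is a change of wording in two table rows and a few lines of code, with no new data. The real drawback is that a mean is less stable than a median in small diagnosis groups. At CV 1.0 the 95% half-width, 1.96 × CV/√n, is 36% of the mean with 30 donors, 28% with 50 and 20% with 100. The standard error with 30 donors is 1.0/√30 = 18%, still below the 29-31% bias of the median at that CV. At CV 0.5 it is 0.5/√30 = 9%, about equal to the 8-11% bias, so there the gain from the change is small.

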### Data analysis

The data analyses will be performed using STATA software (StataCorp. 2019. State Statistical Software: Release 16. College Station, TX: StataCorp. LLC). For the within-trial cost-effectiveness analysis, two incremental cost-effectiveness ratios (ICERs) will be calculated to evaluate the incremental cost per QALY and the incremental cost per 1 mmHg reduction in systolic blood pressure.

The ICER formula is given below:

$$\begin{array}{l} ICER=\frac{\;Cost_{SINEMA}-Cost_{Usual\;care}}{Effect_{SINEMA}\;-Effect_{Usual\;care}\;} \end{array}$$

Multivariable or multilevel models (with levels defined as villages considering the cluster design) will be employed to explore factors associated with health resource use, cost, and effectiveness. Generalized linear regression modeling of costs with gamma distributions and log linked for multivariable analyses that adjust for age, gender, stroke type, and length of stay will be performed.

Several sensitivity analyses will be considered to quantify the level of decision uncertainty. Deterministic sensitivity analyses will be performed on chosen variables to identify key determinants for the results, as presented in Table 2. We will generate cost-effectiveness scatterplots to explore the uncertainties around incremental costs and effectiveness. A cost-effectiveness acceptability curve (CEAC) will be created to explore the probabilities of the SINEMA intervention being cost-effective at a range of cost-effectiveness thresholds.

**Table 2 T2:** Sensitive analysis of key indicators.

	**Base case**	**Range**

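### In Table 2, the missing outpatient and medication cost rows take their base case from one reference group and their range from another

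*Protocol article*

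**What the plan says.** The Data analysis section states: "Deterministic sensitivity analyses will be performed on chosen variables to identify key determinants for the results, as presented in Table 2". Three cost rows of Table 2 deal with missing values.

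- Inpatient care at other facilities. Base case: "Median inpatient cost for same or similar diagnosis". Range: "25%, 75% percentile of inpatient cost for those who were hospitalized with same or similar diagnosis".
- Outpatient cost. Base case: "Mean outpatient cost for same or similar diagnosis". Range: "25%, 75% percentile of outpatient cost for those who were hospitalized with same or similar diagnosis".
- Medication, labelled "Missing information on medication cost of daily doses". Base case: "Mean cost for the conventional drugs". Range: "25%, 75% percentile of medication cost for those who took same or similar drugs".

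Elsewhere, the section on resources used for healthcare services prices medication at a standard unit cost by type of drug. Table 1 takes medication quantity from self-reported use and adherence in the follow-up survey, and marks the source for outpatient cost as estimated.

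**The concern.** In a one-way sensitivity analysis of an imputed cost, the range should express how uncertain the imputed value is. That requires base value and limits to describe the same distribution. In the outpatient and medication rows the two columns name different groups.

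Two things are at stake. First, the base-case column supplies the values that enter the main ICERs, so the choice of group affects more than the sensitivity analysis. Second, Table 2 is meant to show which inputs drive the result. If the group changes between columns, part of any movement in the ICER comes from that change, and an input may look influential, or harmless, for the wrong reason.

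The medication row raises a further point. Where the drug is known and only its daily dose is missing, one mean over an unspecified set of drugs sets aside information already collected and departs from the plan's own valuation by type.

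**Working it through.** The article gives no cost, spread or missing share for these rows, so there is no stated figure to reproduce. The check compares the wording and then asks how large a gap between groups would matter.

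**Wording.**
- Inpatient: both columns rest on the same or a similar diagnosis. The restriction to hospitalised people in the range changes nothing, since only they have inpatient costs. The base is a median, which always lies between its own quartiles.
- Outpatient: the same restriction appears in the range only. Here it does change the group, because people can have outpatient costs without being admitted.
- Medication: the base refers to conventional drugs, a term used nowhere else in the article; the range refers to users of the same or similar drugs. Nothing says that the two sets coincide.

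**When does a base value leave the range?** Let m be the mean in the group that supplies the range, and r the base value divided by m. The base is outside when r < Q1/m or r > Q3/m.

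For a lognormal cost, with s² = ln(1 + CV²):
- Q1/m = exp(−0.6745s − s²/2)
- Q3/m = exp(0.6745s − s²/2)

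Example at CV 0.5: s² = ln 1.25 = 0.223 and s = 0.472, so Q1/m = exp(−0.319 − 0.112) = 0.65 and Q3/m = exp(0.319 − 0.112) = 1.23.

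For a gamma cost (the family the plan uses in its cost regression), the shape is 1/CV² and the quartiles are divided by the shape. All CVs are assumed.

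| CV | lognormal Q1/m to Q3/m | gamma Q1/m to Q3/m |
|---|---|---|
| 0.3 | 0.79 to 1.17 | 0.79 to 1.18 |
| 0.5 | 0.65 to 1.23 | 0.63 to 1.28 |
| 1.0 | 0.40 to 1.24 | 0.29 to 1.39 |
| 1.5 | 0.27 to 1.15 | 0.08 to 1.29 |
| 2.0 | 0.19 to 1.05 | 0.01 to 1.04 |

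**Different groups, base too high.** The upper limits run from 1.04 to 1.39, so a base value 4% to 39% above m, depending on CV and distribution, passes the upper quartile.

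**Different groups, base too low.** This is the direction to expect for outpatients if hospitalised people cost more. The base falls below the range once the hospitalised mean exceeds the base-case mean by a factor of more than 1/(Q1/m): 1/0.786 = 1.27 at CV 0.3; 1/0.65 = 1.54 at CV 0.5; 1/0.403 = 2.48 at CV 1.0 (lognormal).

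**Same group (r = 1).** The lognormal mean exceeds Q3 only when s²/2 > 0.6745s, that is s > 1.349, or CV > √(exp(1.349²) − 1) = 2.27. For the gamma the threshold is a shape of 0.2335, that is CV > 1/√0.2335 = 2.07.

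**One drug versus the total.** Take two drugs with mean daily costs of 2.0 and 0.5 units, both lognormal with CV 0.5. Their ranges are 1.30 to 2.46 and 0.33 to 0.62. A generic base of 1.0 lies outside both. If one third of the missing doses are for the first drug and two thirds for the second, the mean is 2.0/3 + 2 × 0.5/3 = 1.0 and the aggregate range is 0.65 to 1.23, which contains the base. In aggregate, at this CV, the base falls outside only if the generic mean is more than 23% too high or 35% too low.

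**The case against.** The strongest reply is that this is loose drafting. Conventional drugs may simply mean the usual drugs of the type the participant took. The outpatient range repeats the inpatient row's phrase almost word for word, so it may be a carry-over. A condensed article may also leave such definitions to a fuller plan. Part of this stands: that the medication columns describe different drugs is not established. But these are stated rules rather than omissions, and an analyst who followed them would use different groups. The outpatient restriction needs reconciling even if it is a carry-over.

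A second reply is that other Table 2 rows also differ between columns: adjusted against unadjusted effects, recorded cost against fidelity scenarios, no development cost against a shared one. Those are declared alternatives. The missing-cost rows give percentiles around an imputed value, and such percentiles should come from the distribution that supplied the value.

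Third, errors for dear and cheap drugs can cancel in the total. That stands, as the two-drug example shows.

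A reader might go further in three ways that the article does not support.
- That the ICER can move in one direction only. This requires the aggregate base to lie outside its range, which is not shown.
- That a common drug cost hides a difference in drug choice that SINEMA aims to produce. The Intervention and control section mentions advice on medication use and messages on adherence; it states no aim of changing the type of drug, and Table 1 counts adherence separately.
- That hospitalised people have higher outpatient costs. This is plausible, but no figure is given.

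**Conclusion.** The point holds in a limited form: two of the three missing-cost rows name different reference groups for base case and range, one of them undefined, and nothing else in the article reconciles them. Read literally, the ranges need not bracket their base cases, and the deterministic analysis mixes a change of group with uncertainty. Because the base values also feed the main ICERs, correction is worthwhile.

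The size is unknown. It depends on the share of missing values, the cost gap between groups and the spread of costs, none of which is given; the percentages in the working rest on assumed CVs of 0.3 to 2.0 and on lognormal or gamma costs. It would be wrong to conclude that the base case does lie outside its range. If the medication columns mean the same drugs, that row's mean stays within its quartiles unless the CV exceeds about 2.1 (gamma) or 2.3 (lognormal), and only the wording needs correcting.

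**What to change.** Use one reference group for both columns in each row.

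- Medication: set the base case to the mean daily cost among participants on the same drug, or the same drug class where few take that drug, and take the range from that same group. Drop the term conventional drugs or define it as that group.
- Outpatient: take base case and range from the outpatient costs of participants with the same or a similar diagnosis, without the restriction to those hospitalised.

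Imputing separately by arm is not required. If the observed costs are so skewed that the mean falls outside the quartiles, pair the mean with its confidence interval, or use the median with quartiles as in the inpatient row.

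The cost is a few reworded table cells and a lookup by drug in data already held. The drawback is small groups for rare drugs, which the fallback to drug class handles.

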## Discussion

This manuscript details the study protocol of the economic evaluation that aims to assess the cost-effectiveness of the SINEMA intervention among stroke patients in rural China. As one of a few studies that evaluate the economic value of community-based technology-enabled intervention for stroke prevention and management, this study employs a within-trial evaluation to analyze the incremental cost-effectiveness ratios. If proven cost-effective, the findings from this study will provide robust evidence to policymakers in low- and middle-income countries for adopting and scaling up similar interventions.

Economic evaluation is a crucial component for evaluating the impact of a community-based intervention for disease prevention. Despite the proven effectiveness of the SINEMA intervention, the economic value of the SINEMA intervention will further inform decision-makers on the allocation of scarce resources for stroke prevention and control. Although effective strategies for community-based interventions have been increasingly examined through trials (17–19), only a few studies seek to answer the economic value of the intervention. For instance, the COBRA-BPS trial aimed to assess the effectiveness of community-based interventions for improving blood pressure control in Bangladesh, Pakistan, and Sri Lanka, and the COBIN study targeted lifestyle intervention for blood pressure control in Nepal estimated the long-term economic value through budget impact and cost-effectiveness analysis from the health system perspective (20, 21). However, these assumptions may introduce certain biases which may overestimate the benefit of the intervention (22, 23). Different from these studies, our study performed a within-trial economic evaluation method with individual granularity by using first-hand data collected from the trial. In addition, existing reviews also called for research to consider the uniqueness of measuring the cost and benefit of digital health solutions compared with traditional human-delivered interventions (24). Thus, our study may shed light on the field by detailing our methodology for evaluating the cost-effectiveness of a community-based technology-enabled intervention.

Our study design has several unique features. First, the study measures a multifaceted intervention with digital health components. Digital health interventions have a high potential to deliver interventions to a large-scale population, thus, it holds the promise of improving chronic disease management. Second, compared to human-delivered intervention, the development cost for digital health intervention is relatively high; however, the operation and marginal cost for the implementation could be limited to none if it is scaled to a large population (25). In our protocol, we followed previous studies' methods to evaluate the operational cost of the SINEMA model in our design (11). We also include the development cost in our sensitivity analysis.

As for data collection, due to the constrained funding support, the SINEMA trial observed and measured the cost and effectiveness of the intervention over a 12-month period. Although such follow-up duration was reasonable to measure a high number of stroke cases, the data collected from the trial period hardly provided information about the long-term benefits and impact of the intervention. Instead, we will use data from other trials and cohort studies that were conducted in similar settings to estimate the long-term natural transition of stroke patients in rural China (26, 27). This approach enables us to estimate the long-term economic impact of the SINEMA intervention.

The main limitation of this design lies in the field of cost measurement. First, although we measured key direct health costs at the individual level, we are only able to quantify the inpatient costs and medication costs for participants from the health insurance data. Due to the limited data access, we cannot measure the cost of inpatient care if the patients seek healthcare services beyond the major four hospitals in the study regions, which is likely to happen as there is no referral system that restricts service-seeking behaviors in rural China (27). Therefore, we tend to underestimate the inpatient costs if there are relatively more inpatients in the control group. Second, the analysis may underestimate some of the labor costs. For instance, the village doctors may provide blood pressure assessments during clinic visits for free, and the payment scheme may not be set by the number of services provided at the clinic visits. These visits were not paid, thus were not included in the financial analysis.

